## Abstract

**Background:**

Cognitive behavioral therapy for obsessive-compulsive disorder has been established, but access to this therapy in Japan is limited. Internet-based cognitive behavioral therapy may improve treatment accessibility and sufficiently improve obsessive-compulsive symptoms. There are few randomized controlled trials examining the effectiveness of internet-based cognitive behavioral therapy in patients with obsessive-compulsive disorder. We designed a randomized controlled trial protocol to assess the effectiveness of guided internet-based cognitive behavioral therapy in Japanese patients with obsessive-compulsive disorder.

**Objective:**

We aimed to develop a protocol for a randomized controlled trial of internet-based cognitive behavioral therapy in Japanese patients with obsessive-compulsive disorder.

**Methods:**

The randomized controlled trial will compare internet-based cognitive behavioral therapy treatment and usual care groups, each consisting of 15 participants (n=30) diagnosed with obsessive-compulsive disorder. We will evaluate the effectiveness of a 12-week intervention. The primary outcome of symptom severity will be measured using the Yale-Brown Obsessive-Compulsive Scale. Secondary outcomes will be assessed with the Obsessive-Compulsive Inventory, Beck Anxiety Inventory, Patient Health Questionnaire-9, Generalized Anxiety Disorder-7, Working Alliance Inventory-Short Form, and the Euro Qol – 5 Dimension. All measures will be assessed at weeks 0 (baseline) and 12 (follow-up). In the statistical analysis comparing treatment effects, the least-squares means and their 95% CIs will be estimated by analysis of covariance with the change in total outcomes scores at week 12. All comparisons are planned, and all *P* values will be two-sided, with values <.05 considered statistically significant.

**Results:**

The study will be performed from January 2020 to March 2021, and results are expected to be available in mid-2021.

**Conclusions:**

The trial will demonstrate whether internet-based cognitive behavioral therapy improves access and is more effective than more usual care for patients with obsessive-compulsive disorder in Japan.

**Trial Registration:**

University Hospital Medical Information Network (UMIN) 000039375; https://upload.umin.ac.jp/cgi-open-bin/ctr/ctr_view.cgi?recptno=R000044422

**International Registered Report Identifier (IRRID):**

DERR1-10.2196/18216

### Internet-Based Cognitive Behavioral Therapy for Obsessive-Compulsive Disorder

Previous randomized controlled trials for obsessive-compulsive disorder have been performed in Sweden, the United States, and Korea [10-12]. In a previous randomized study of 101 patients with OCD assigned to ICBT and online supportive psychotherapy followed by blinded assessments [10], ICBT showed significant improvements in the intervention group compared to the control group. Obsessive-compulsive symptoms as measured by the Yale-Brown Obsessive-Compulsive Scale (Y-BOCS) were improved, and the effect size was high (Cohen *d*=1.12). Another study of 56 patients with OCD included ICBT, reading therapy, and waiting groups [11]. The results of that study suggested that ICBT has a large effect size (Cohen *d*=1.57) among the waiting group at pre- and post- treatment. In Asia, a Korean research team conducted a randomized controlled trial and reported that the treatment group showed significantly improved symptoms over the waiting group, and 25.9% (17/42) responded to treatment, with a within-group effect size of 1.64 (Cohen *d*) [12]. Thus, ICBT, like face-to-face CBT [13], has been shown to be highly effective in the treatment of OCD.

More clinical trials are needed to draw general conclusions regarding the efficacy of ICBT because of substantial country-to-country variations in cultural background, the spread of information, availability of communication equipment, and literacy. Prior research has been performed in countries where the environment is conducive to ICBT, especially as developed countries have a well-established computerized social infrastructure [14]. The penetration rate of information and communication equipment in Japan is more than 90% of all households [15], and there is a favorable social infrastructure for verifying the effectiveness of ICBT. In Japan, our research team confirmed that all patients were in remission by conducting CBT on 3 patients with OCD in their 20s and 40s in the ICBT case series [9]. Based on this achievement, we developed an ICBT program that includes an electronic learning (e-learning) system and chat app. From January 2020 to March 2021, we are conducting a randomized controlled clinical trial in patients diagnosed with OCD.

### Objective

This paper describes the study protocol for a randomized controlled trial designed to evaluate the clinical effectiveness of ICBT versus usual care (UC) among patients diagnosed with OCD.

## Methods

### Study design

This study was designed as a prospective blinded randomized trial with two parallel intervention groups consisting of a 12-week treatment regime of UC alone or ICBT combined with UC (Figure 1) [15-18].

**Figure 1 figure1:**
[figure not shown]
CONSORT flow diagram of a parallel randomized trial with two groups.

#### Participants and Eligibility Criteria

Inclusion criteria for this study include individuals aged 15-60 years having a primary diagnosis of OCD according to the Mini-International Neuropsychiatric Interview (MINI) and remaining symptomatic [19,20] with symptoms rated at least moderate in severity, based on a Y-BOCS score >14 [21,22], and with sufficient skills to send email and access the e-learning system. Participants with psychosis or organic mental disorder, or with a current high risk of suicide, substance abuse or dependence within the 12 months prior to enrollment, antisocial personality disorder, or unstable medical conditions will be excluded.

#### Recruitment

The planned recruitment rate is 3 participants per month from January 2020 to December 2020, or until a total of 30 participants are recruited. Participants will be recruited by placing informational posters and leaflets at medical institutions in Chiba and Fukui Prefecture and on the institutional homepage. All participants will continue to be treated by their general practitioners, whose permission must be granted prior to study enrollment. This study will be conducted at the outpatient clinic of Chiba University Hospital and Fukui University Hospital in Japan.

### Interventions

#### Guided ICBT program

The ICBT program participants will engage in one program learning session per week. After working on the ICBT, the patient will email the therapist about their thoughts and questions about the study and behaviors suggested by the program for them to try in daily life. The therapist, as general rule, will contact the patient within 24 hours to encourage the patient's efforts, raise questions, and advise on CBT techniques to increase the effectiveness of treatment. The ICBT program consists of 12 weekly lessons, including the following elements: ICBT program guidance, psychological education and case conceptualization of obsessive-compulsive disorder, setting treatment goals and creating an anxiety hierarchy, explaining the behavioral experiment of catastrophic interpretation and the exposure-response disturbance method, and preventing recurrence.

#### Software

We will use LearningBox, a system developed by Tatsuno Information Systems [23] and MediLine, a medical chat service developed by Shar Medical to provide ICBT [24]. LearningBox (Multimedia Appendix 1) is an e-learning system that allows administrators to easily create and manage educational materials, manage members, and save and view grades. Video and PDF teaching materials can also be posted on the site and distributed to specific users. The e-learning system can store and manage user results, but personal information is not stored during the present trial.

MediLine (Multimedia Appendix 2) is a medical chat service (medical social networking service) that replaces email and phone calls. It has strong encryption against military-level information leaks. MediLine communicates in a double-encrypted state according to the Japanese government guidelines [25-28]. Encryption is performed end-to-end in real time in the server, during communication, and in temporary memory at the terminal. In other words, it is designed so that information cannot be extracted during data transfer. Since identifiers are issued by in-house introduction, hijacking and spoofing are prevented. The staff registered by the organization can delete the account at the time of retirement and cannot view it thereafter, so there is no provision for information to be taken out of the hospital after retirement [24].

#### Usual Care (Control group)

Participants will be permitted to continue using antidepressant or other medicines during the study period. Participants' primary doctor will have right to change medication, to refer participants for counselling, and to secondary care if deemed clinically appropriate. All changes in conventional treatment, along with the reasons for those changes, will be recorded. Participants in the control group will be offered the ICBT treatment after the trial if they did not improve under the control conditions.

### Outcomes

#### Baseline and Clinical Characteristics

Baseline characteristics will include gender, age, educational attainment, marital status, employment status, age at onset and duration of OCD, medications, and intelligence as measured by the Japanese Adult Rating Test (JART) [29,30].

#### Primary Outcome

The primary outcome will be measured by the Y-BOCS, which is a rated questionnaire consisting of 10 questions across two subscales, Obsession and Compulsion [21,22].

#### Secondary Outcomes

Secondary outcomes will include health-related quality of life, symptoms of depression and generalized anxiety, and therapeutic relationship. We will measure health-related quality of life with the EuroQol - 5 Dimension (EQ-5D) [31,32], the psychological bond between therapist and participant using the Working Alliance Inventory-Short Form (WAI-SF) [33], depressive symptoms using the Patient Health Questionnaire-9 (PHQ-9) [34], generalized anxiety symptoms using the Generalized Anxiety Disorder-7 (GAD-7) [35], and the Beck Anxiety Inventory (BAI) [36].

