### Statistical Analysis Plan

Statistical analysis and reporting will be conducted in accordance with CONSORT (Consolidated Standards of Reporting Trials) guidelines [38], with primary analyses based on the intention-to-treat principle. For baseline variables, summary statistics will be constructed, employing frequencies and proportions for categorical data and mean and SD for continuous variables. Baseline variables will be compared using the Fisher exact test for categorical outcomes and the unpaired *t*-test for continuous variables. For the primary analysis comparing treatment effects, the least-squares means and their 95% CIs will be estimated by analysis of covariance (ANCOVA) with the change in total Y-BOCS scores at week 12. This ANCOVA model will account for the variation caused by treatment effects, and gender and baseline Y-BOCS scores will be entered as covariates. Analyses of secondary outcomes will be performed in the same manner. All comparisons are planned, and all *P* values will be two-sided. *P* values <.05 will be considered statistically significant. All statistical analyses will be performed using the latest version of SAS (SAS Institute Inc).

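### The week-0 schedule and the between-arm change analysis do not fit the WAI-SF, because the only therapist described belongs to the ICBT program and is contacted once program work begins

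*Protocol article*

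**What the plan says.** The Abstract (Methods) names the WAI-SF among six secondary measures: "Working Alliance Inventory-Short Form, and the Euro Qol" closes the list. The schedule follows directly: "All measures will be assessed at weeks 0 (baseline) and 12 (follow-up". The same paragraph says that treatment effects will be "estimated by analysis of covariance with the change in total outcomes scores at week 12".

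The Secondary Outcomes section describes the instrument as measuring "the psychological bond between therapist and participant using the Working Alliance Inventory-Short Form (WAI-SF".

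The Statistical Analysis Plan section sets out the primary ANCOVA of week-12 change, in which "gender and baseline Y-BOCS scores will be entered as covariates" alongside treatment. It then says: "Analyses of secondary outcomes will be performed in the same manner". No section exempts the WAI-SF from the schedule or from the model, restricts it to one arm, or says which clinician is to be rated.

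The arms are "a 12-week treatment regime of UC alone or ICBT combined with UC". The therapist appears in the section on the guided ICBT program, where the participant writes to the therapist after working on a lesson. The Usual Care section leaves control participants with their primary doctor, who may refer them for counselling or to secondary care. It offers ICBT to controls only after the trial, and only to those who have not improved.

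**The concern.** A working-alliance score describes a relationship with a particular person. A change score makes sense if the same relationship is rated at both times, and an arm contrast makes sense if the same kind of relationship is rated in both arms. The symptom and quality-of-life scales meet both conditions, because each participant rates their own state. The WAI-SF does not meet them under these general rules.

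What is at stake is a secondary P value. If controls rate their doctor and ICBT participants rate the ICBT therapist, the model will run and return an estimate with a confidence interval. A significant result could then be reported as a benefit of ICBT when it mainly reflects that one arm was assigned a therapist. If controls leave the form blank, the planned contrast cannot be estimated.

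**Working it through.** The plan gives no figure to reproduce here. The check sets the schedule, the analysis rule and the description of the arms side by side.

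**Step 1. Who can be rated in each planned cell.** Two arms at two times give 2 × 2 = 4 cells.

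| Arm | Week 0 | Week 12 |
|---|---|---|
| ICBT + UC | Own doctor, or another existing clinician; contact with the ICBT therapist has not begun | ICBT therapist (or own doctor) |
| UC alone | Own doctor, or another existing clinician | Own doctor, or a counsellor if referred |

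The ICBT therapist can be the person rated in 1 of the 4 cells. With the planned 15 participants per arm and complete follow-up, that is 15 of 4 × 15 = 60 planned ratings. The other 45 can refer only to someone else, or be left blank.

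**Step 2. What the change score would be.** Write T for the bond with the ICBT therapist and D for the bond with the participant's own doctor or other clinician, with the week as subscript.

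- ICBT arm, if the ICBT therapist is rated at week 12: change = T₁₂ − D₀. This subtracts a rating of one person from a rating of another.
- UC arm: change = D₁₂ − D₀.

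**Step 3. What the ANCOVA would estimate.** Randomization makes the expected D₀ equal in the two arms, so it cancels from the expected difference:

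E(T₁₂ − D₀ | ICBT) − E(D₁₂ − D₀ | UC) = E(T₁₂ | ICBT) − E(D₁₂ | UC).

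The treatment effect is then the mean bond with an ICBT therapist minus the mean bond with a doctor or counsellor. Adjusting for gender and baseline Y-BOCS does not alter this. It compares two kinds of clinician, and does not show how a therapeutic relationship changed under treatment.

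**Step 4. The other ways of completing the form.**

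- Only ratings of the ICBT therapist are accepted: the three remaining cells are empty. There is no change score in either arm and no control mean, so the contrast cannot be estimated.
- Everyone rates their own doctor at both times: change is D₁₂ − D₀ in both arms, and the contrast is coherent. But it asks whether ICBT alters the relationship with the doctor and leaves out the therapist who delivers the intervention. The article does not say that this is intended.

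No reading yields a between-arm change in the bond with the therapist who delivers ICBT.

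**The case against.** The strongest reply is that the conflict is put together from general sentences. No sentence specifically places the WAI-SF at week 0 or says that it is compared between arms. The schedule stands only in the Abstract, and the analysis rule is one generic line. A journal article condenses a fuller protocol, and details such as who completes an instrument and whom they rate are often left to that document.

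Part of this stands. The article may simply have omitted an exemption that exists elsewhere. But the point does not rest on missing detail. The article states a schedule for all measures immediately after a list that names the WAI-SF, and states an analysis rule for secondary outcomes without exception. Applied to this instrument, both rules give something that cannot be interpreted as intended.

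A reader might go further and infer that all week-0 ratings and all usual-care ratings have no valid person to refer to, so that the scores are void. The documents do not support that. The Secondary Outcomes section says therapist, not study therapist or ICBT therapist. The Recruitment section says that all participants continue with their general practitioners, and the Usual Care section allows referral for counselling. A clinician can therefore be rated in every cell. The difficulty is that it cannot be the same clinician, or the same kind of relationship, as the one rated in the ICBT arm at week 12.

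It is also fair to say that harm is conditional: a misleading P value arises only if controls rate someone else, not if they leave the form blank.

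**Conclusion.** The point holds in this limited form: as stated, the general schedule and analysis rule do not suit the WAI-SF, and the resulting change score and arm contrast would not measure one relationship. It affects one of the six secondary measures listed in the Abstract (the Secondary Outcomes section names five, without the Obsessive-Compulsive Inventory). The primary Y-BOCS comparison, the sample size and the randomization are untouched, so this is a correction that should be made and not a threat to the trial.

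The conclusion rests on two assumptions. The first is that the sentences about all measures and about secondary outcomes include the WAI-SF, as nothing exempts it. The second is that no ICBT therapist has a working relationship with a participant before week 0, as the program description implies. If the full protocol names the clinician to be rated, or confines the instrument to the ICBT arm, the article's wording still needs to be brought into line with it.

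**What to change.** Exempt the WAI-SF from the week-0 assessment and from the between-arm ANCOVA of change. Collect it in the ICBT arm at week 12, with the ICBT therapist named as the person rated. Report it descriptively (mean and SD) as a process measure. Label any association with Y-BOCS change exploratory; with about 15 participants it could not be more.

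A smaller change would be to state which clinician is rated in each arm and at each time. That would make the scores definable. But a contrast between an ICBT therapist and a doctor would still compare different relationships and should not carry a P value as a treatment benefit.

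The cost is a change of wording in the schedule and the analysis section, and one fewer comparative secondary outcome. Participants complete fewer forms.

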### Sample Size

We used the statistical analysis software G*power 3.1 to estimate sample size of an unmatched t-test [37]. Sample size was estimated as 14 participants per group. The effect size predicted in this study is at least 1.00 from the two previous two clinical trials [8-10], the directionality of the test is a two-sided test, the significance level was set at 0.05%, the test was two-sided, and the test power (1-β) was set to 80%. The study will require a minimum 14 participants per group so we are setting a target enrollment of 30 participants to allow for a 5% dropout rate.

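### Fourteen per group gives about 72% power, not 80%, for the stated two-sided t-test at an effect size of 1.00

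*Protocol article*

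**What the plan says.** The Sample Size section sets out a complete calculation.

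- Method: "We used the statistical analysis software G*power 3.1 to estimate sample size of an unmatched t-test".
- Effect size: "The effect size predicted in this study is at least 1.00".
- Sidedness: "the directionality of the test is a two-sided test". The same sentence says two-sided a second time.
- Level: "the significance level was set at 0.05", printed with a percent sign after the figure.
- Power: 80%.
- Result: "Sample size was estimated as 14 participants per group", repeated as "The study will require a minimum 14 participants per group".

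Enrolment is then raised to 30 to cover 5% dropout, and the abstract carries this forward as 15 per group. The Randomization section fixes 1:1 allocation. The Statistical Analysis Plan section makes all P values two-sided, and P "values <.05 will be considered statistically significant". It names ANCOVA on the change in Y-BOCS at week 12 as the primary analysis, with gender and baseline Y-BOCS as covariates.

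**The concern.** Every input the calculation needs is printed, so the result can be checked directly, and 14 per group looks too small for a two-sided 5% test at an effect of 1.00. This is not a detail left to a fuller document: the article prints both the inputs and the output, and they disagree.

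This paragraph is the trial's only stated justification for its size. If the power is lower than claimed, a non-significant primary result will be judged against a chance of success that the stated calculation does not support. In a trial of 30 people, that matters for how a null finding is read.

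**Working it through.** **Inputs.** From the Sample Size section: d = 1.00, two-sided, power 80%, unpaired t-test. From the Randomization section: equal groups. The level is taken as 0.05. The Sample Size section prints it with a percent sign, but the Statistical Analysis Plan section uses P < .05. The 0.05 reading is the one more favourable to the plan.

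**Formula.** With n per group, df = 2n − 2 and the noncentrality parameter is δ = d·√(n/2). Two-sided power is P(T > t_crit) + P(T < −t_crit), where T is noncentral t with parameters df and δ, and t_crit is the 0.975 quantile of the central t distribution. This is the exact calculation that the named software performs for this test.

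**The plan's figure.** At n = 14, df = 26, δ = √7 = 2.646 and t_crit = 2.056. Power is 72.1%, so the claimed 80% is not reproduced.

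**Power by group size, d = 1.00, level 0.05**

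| n per group | Two-sided | One-sided |
|---|---|---|
| 13 | 68.7% | 79.7% |
| 14 | 72.1% | 82.4% |
| 15 | 75.3% | 84.8% |
| 16 | 78.1% | 86.8% |
| 17 | 80.7% | 88.6% |

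The smallest n reaching 80% is 17 for the two-sided test and 14 for the one-sided test.

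**Other routes to 14**

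- *Normal approximation.* The two-sided test needs 16 per group and has 75.4% power at 14. The one-sided test needs 13. Neither gives 14.
- *A larger effect.* A two-sided test at d = 1.12 needs 14 per group (81.4% power). The Introduction reports 1.12 for one earlier trial, but the Sample Size section states 1.00.
- *The level as printed.* At 0.05% (0.0005) two-sided, power at 14 is 12.9% and 41 per group are needed.

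**Smallest effect with 80% two-sided power.** d = 1.10 at 14 per group and d = 1.06 at 15 per group.

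**Dropout.** 28/0.95 = 29.5, so 30. This step is correct given 14 per group. From 17 per group it would be 34/0.95 = 35.8, so 36.

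**What the ANCOVA might recover.** The documents give no correlation r between baseline and week-12 Y-BOCS, so r is an assumption. If d = 1.00 is standardised on the week-12 SD, adjustment raises the effective effect to 1/√(1 − r²). With 14 per group and df = 28 − 4 = 24, power is:

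| r | Power |
|---|---|
| 0.3 | 75.8% |
| 0.4 | 79.1% |
| 0.5 | 83.4% |
| 0.6 | 88.7% |

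Power crosses 80% at r of about 0.42. With 15 per group it crosses at about 0.34.

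**The case against.** The strongest reply is that the primary analysis is not the t-test. An ANCOVA adjusting for baseline Y-BOCS may well reach 80% with 14 per group, and only a moderate correlation is needed. This stands as far as it goes: the check shows that the printed justification fails, not that the planned analysis must be underpowered. But the plan gives no correlation and rests its number on an unadjusted t-test, so the gain cannot be credited to the calculation as written.

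A second reply concerns the cause. Nothing says that a one-sided option was chosen, and an effect of 1.12, which the Introduction cites, would also give 14 two-sided. That is fair, and the cause remains open. It does not rescue the paragraph: if 1.12 was entered, the stated effect size is wrong instead. Nor does describing 1.00 as a minimum help, since a power claim has to hold at the smallest effect it names.

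Third, taking the level as 5% is a reading of a misprinted figure. This is true, but the literal reading makes the shortfall far larger.

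Finally, the harm is limited. The analysis model, test level and type I error are unaffected, and the planned 95% confidence intervals would show the imprecision. That bears on the consequences, but the stated sample size and power remain wrong as printed.

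**Conclusion.** The concern holds. At d = 1.00, two-sided 5%, 14 per group gives 72.1% power against a claimed 80%, so the type II error is 27.9% rather than 20%. The stated inputs need 17 per group, which is three more per group and six more evaluable participants in total. Full retention of all 30 gives 75.3%.

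This rests on the unpaired t-test that the section names, equal groups, and a level of 0.05 taken from the Statistical Analysis Plan section. The power of the planned ANCOVA could lie on either side of 80%, depending on a correlation the article does not give. A one-sided setting would explain the 14 exactly, but that is an inference, and the mismatch does not depend on it.

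**What to change.** Correct the Sample Size paragraph in one of two ways.

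- **(a) Keep 30 and restate the power.** Report about 72% two-sided power at d = 1.00 with 14 evaluable per group, and say that 80% is reached only for d of about 1.10 or more.
- **(b) Keep 30 and base it on the ANCOVA.** State the assumed baseline-to-week-12 correlation, its source, and the SD on which d is standardised. If that is the week-12 SD, 80% power at 14 per group needs a correlation of about 0.42 or more.

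In either case, print the level as 0.05 or 5% so that it agrees with the analysis section. If a different effect size or a one-sided setting was actually entered, say so.

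The cost is one rewritten paragraph and, under (a), a less favourable power figure. Neither option needs more patients. Holding 80% on the unadjusted t-test at d = 1.00 would instead mean enrolling 36.

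### The sample size section gives the significance level as 0.05%, which conflicts with the two-sided P<.05 rule and leaves the stated 14 per group impossible to reproduce as printed

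*Protocol article*

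**What the plan says.** All references are to the protocol article.

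- **Sample Size, test and software:** "We used the statistical analysis software G*power 3.1 to estimate sample size of an unmatched t-test".
- **Sample Size, effect:** "The effect size predicted in this study is at least 1.00", attributed to earlier trials.
- **Sample Size, sidedness:** "the directionality of the test is a two-sided test". The same sentence then says two-sided a second time.
- **Sample Size, level:** "the significance level was set at 0.05", with a percent sign after the figure.
- **Sample Size, power:** "the test power (1-β) was set to 80", again with a percent sign.
- **Sample Size, result:** 14 per group, raised to 30 in total for 5% dropout.
- **Statistical Analysis Plan, decision rule:** P "values <.05 will be considered statistically significant", with all P values two-sided.
- **Statistical Analysis Plan, estimation:** "the least-squares means and their 95% CIs will be estimated by analysis of covariance (ANCOVA"), so the confidence level corresponds to a two-sided 0.05 test.
- **Abstract, Methods:** P "values will be two-sided, with values <.05 considered statistically significant".

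**The concern.** A level of 0.05% is an alpha of 0.0005. The decision rule uses 0.05, and 0.05/0.0005 = 100. The article describes no multiplicity adjustment and no interim look that would explain sizing the trial at a stricter level than the one at which it will be tested.

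The significance level is one of the four inputs that determine the sample size, along with sidedness, effect size and power. If it is printed wrongly, a reader cannot check the number of participants from the article. The slip also hides a second question that arises once it is put right: whether 14 per group gives the claimed 80% power at the stated effect. What is at stake is the traceability of the sample size and the accuracy of the power statement. The rule for judging the primary outcome is not in doubt.

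**Working it through.** **Inputs (Sample Size section):** unpaired t-test, equal groups, two-sided, standardized effect d = 1.00 (the stated minimum), power 80%, level printed as 0.05%, result 14 per group. Equal allocation is confirmed under Randomization.

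**Formula.** With n per group, df = 2n − 2 and the noncentrality parameter is λ = d·√(n/2). Two-sided power is P(|T| > t₁₋α/₂,df), where T is noncentral t(df, λ). This is the standard power calculation for the named test.

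**Step 1. The plan's figure with its inputs as printed (alpha 0.0005, two-sided, d = 1.00).**
- n = 14: df = 26, λ = 1.00·√7 = 2.646, critical value 3.974, power 12.9%.
- n = 15: power 15.2%.
- n = 40: power 79.3%. n = 41: power 80.9%.

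The requirement is 41 per group (40.4 before rounding). The stated 14 is not reproduced.

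**Step 2. The same calculation at the level of the decision rule (alpha 0.05, two-sided, d = 1.00).**
- n = 14: λ = 2.646, critical value 2.056, power 72.1%.
- n = 15: df = 28, λ = 1.00·√7.5 = 2.739, critical value 2.048, power 75.3%.
- n = 16: power 78.1%. n = 17: power 80.7%.

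The requirement is 17 per group (16.7 before rounding), or 16 by the normal approximation, which is not the stated method. Correcting the percentage brings the calculation much closer to 14 but does not reach it.

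**Step 3. What would give 14 per group at 80% power?**

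| Level | Sides | d | n per group before rounding | n per group | Power at 14 |
|---|---|---|---|---|---|
| 0.05 | one | 1.00 | 13.1 | 14 | 82.4% |
| 0.05 | two | 1.12 | 13.5 | 14 | 81.4% |
| 0.0005 | two | 1.12 | 32.8 | 33 | not needed |

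At two-sided 0.05, the smallest effect with 80% power at 14 per group is d = 1.10; at 15 per group it is 1.06. The value 1.12 is the effect that the Introduction reports for one of the trials cited in the Sample Size section. At two-sided 0.0005, 14 per group would need d = 1.85.

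**Step 4. The dropout step.** 28/0.95 = 29.5, rounded up to 30. This reproduces, so the discrepancy lies in the 14, not in the allowance for dropout.

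**The case against.** The strongest reply is that this is a misplaced percent sign with no effect on the trial. The Sample Size section supplies a planning input, not a decision rule. The rule appears twice, in the abstract and in the Statistical Analysis Plan section, both times as two-sided P<.05 and both times with 95% confidence intervals. The stated 14 per group is itself evidence that 0.0005 was never used. All of this stands.

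Two stronger readings are therefore not supported:

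- A reader might infer that the decision threshold itself is stated two ways, so that the trial would almost certainly be negative. No text says that the outcome will be judged at 0.0005. The 12.9% and 41 per group show that the printed level cannot be the one used; they do not forecast the power of this trial.
- A reader might infer that 14 per group fits only a one-sided test. That holds only if d is exactly 1.00. The section says at least 1.00, and with the cited 1.12 a two-sided 5% test also needs 14. The article does not say which value was entered, so a one-sided calculation is possible but not shown.

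It can also be said that the power shortfall is a separate matter from the percent sign. In part that is right. But anyone who corrects the level has to restate what the planned number achieves at it, because the sentence would otherwise still pair 14 per group with 80% power at an effect of 1.00. What does not stand is the suggestion that nothing needs doing: the level is printed wrongly, and it is an input on which the sample size depends.

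**Conclusion.** The point holds as an error in a stated sample size input. The printed level is 100-fold below the level used everywhere else in the article, very probably through a unit slip for 5%. The operative rule is two-sided P<.05, so the primary test, its confidence interval and the reading of the result are unaffected.

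The consequence is that the sample size cannot be reproduced as printed: the inputs lead to 41 per group against a stated 14. At the corrected level and d = 1.00, power is about 8 percentage points below the stated 80% with 14 per group (72.1%) and about 5 points below with 15 (75.3%). If the effect entered was about 1.10 or larger, the 80% is correct at 14 per group and only the printed effect size needs clarifying.

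These figures rest on the unpaired t-test that the article names for sizing. The planned covariance analysis adjusts for baseline score and could have more power, but the article gives no baseline-to-outcome correlation from which to compute a gain. The 75.3% also assumes that all 30 participants provide data. With 5% dropout, 30 × 0.95 = 28.5, and the figure for 14 per group is the closer guide.

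**What to change.** In the Sample Size section, replace the printed 0.05% with 5% (two-sided alpha = 0.05). Then make the rest of the sentence agree with it in one of two ways:

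1. Keep d = 1.00 and restate the power: 72.1% with 14 per group and 75.3% with 15, in place of 80%.
2. If a larger effect was entered in the software, state that value and its source. At two-sided 5%, 14 per group supports 80% power from d of about 1.10 upward.

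The saved software input, if kept, would settle which applies, including whether the one-sided option was selected. The cost is one corrected figure and one revised sentence. No change to enrolment, analysis or conduct is required.
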